### Sample size

The sample size for each tumour population has been calculated based on an overall 95% plan acceptability rate, with a CI which is no wider than±5% in absolute terms around this figure This rate is considered necessary to support implementation of the software as the clinical community would be unlikely to accept a lower plan acceptability rate of, for example, 80%.

To achieve at least 90% power that the lower confidence limit for the acceptability plan will be greater than 90%, assuming alpha=0.05 (or one-sided 0.025) and a binomial distribution, the required sample size is approximately 330 for each tumour population.^37^

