**Methods:**

ARCHERY is a non-randomised prospective study to evaluate the quality and economic impact of AI-based automated radiotherapy treatment planning for cervical, head and neck, and prostate cancers, which are endemic in LMICs, and for which radiotherapy is the primary curative treatment modality. The sample size of 990 patients (330 for each cancer type) has been calculated based on an estimated 95% treatment plan acceptability rate. Time and cost savings will be analysed as secondary outcome measures using the time-driven activity-based costing model. The 48-month study will take place in six public sector cancer hospitals in India (n=2), Jordan (n=1), Malaysia (n=1) and South Africa (n=2) to support implementation of the software in LMICs.

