### Statistical analysis plan

We will fit a logistic regression model to the binary outcome of plan acceptability adjusted by the centre with cluster robust SEs. We calculate the overall marginal proportion estimate balanced for the centre, to calculate the robust CI that maintains the family-wise error rate at 0.05. An additional analysis will investigate the inter-rater agreement for the plan. For each cancer, this will be assessed by calculating the kappa statistic between the first two expert raters assessing plans, so excluding the conditional third rating.

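### The stated 90% power is calculated for 330 independent, equally weighted plans and is unsupported for the centre-adjusted, cluster-robust, centre-balanced analysis that is planned

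*Protocol article*

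**What the plan says.** The Sample size section sets the target for each tumour type: true acceptability 95%, at least 90% power for the lower confidence limit to exceed 90%. It gives the basis as "assuming alpha=0.05 (or one-sided 0.025) and a binomial distribution, the required sample size is approximately 330 for each tumour population". The abstract repeats the result: "The sample size of 990 patients (330 for each cancer type) has been calculated based on an estimated 95% treatment plan acceptability rate". Neither place mentions an intracluster correlation (ICC), a design effect, the number of centres or their expected sizes.

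The Statistical analysis plan section describes a different analysis of the same outcome: "We will fit a logistic regression model to the binary outcome of plan acceptability adjusted by the centre with cluster robust SEs". It continues: "We calculate the overall marginal proportion estimate balanced for the centre", from which a robust confidence interval is taken.

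The abstract names six hospitals in four countries. The Patient exclusion criteria section says that consecutive eligible patients will be approached. The article gives no recruitment target or cap per centre.

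**The concern.** A power statement belongs to a particular estimator and interval. This one belongs to a simple proportion of independent plans, each with the same weight. The planned analysis departs from that in up to three ways, each of which can widen the interval:

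- Cluster-robust standard errors allow for correlation of plans within a cluster, most naturally the centre.
- Balancing over centres, read as equal centre weights, loses precision when centres recruit unequally.
- Six clusters are few. A robust interval that keeps its error rate with six clusters needs a wider multiplier than 1.96.

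The Introduction itself calls the centres diverse and says that they differ in technical and workforce infrastructure. The conclusion for each tumour type depends on the lower limit clearing 90%, and the Dissemination section makes roll-out depend on the objectives being met. If the real power is well below 90%, software that truly reaches 95% could miss the target more often than the sponsor expects.

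**Working it through.** **Inputs from the protocol article.** p0 = 0.90, p1 = 0.95, one-sided alpha 0.025, power at least 0.90, n = 330 per tumour type (Sample size); six centres (abstract). The average is 330/6 = 55 plans per centre, if every centre recruits every tumour type.

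**Inputs assumed.** The article gives no ICC and no centre sizes. ICC values of 0.005, 0.01 and 0.02 are assumed. At p = 0.95 the between-centre SD is √(ICC × 0.95 × 0.05), i.e. 1.5, 2.2 and 3.1 percentage points. The recruitment patterns below are also assumed.

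**1. The plan's own figure.**

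- Normal approximation: n = [1.96√(0.90 × 0.10) + 1.2816√(0.95 × 0.05)]² / 0.05² = 301; with continuity correction, 321.
- Exact binomial at n = 330: the lower limit exceeds 90% when at least 308 plans are acceptable. P(X ≥ 308 | 0.95) = 0.930 and P(X ≥ 308 | 0.90) = 0.0224.
- Exact power stays at or above 90% from n = 316. The spare sample is 330/316 = 1.04, about 4%.

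So 330 is right for independent, equally weighted plans.

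**2. Fixed centres, equal centre weights, no clustering.** Effective n = 36 / Σ(1/n_j). Power at the effective n is given by the normal approximation and the exact binomial. Simulated power uses z limits with the within-centre binomial standard error.

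| Recruitment | Effective n | Power at effective n | Simulated, logit scale | Simulated, proportion scale |
|---|---|---|---|---|
| 55 × 6 | 330 | 93% | 93% | 96% |
| 100/80/60/40/30/20 | 36/0.1475 = 244 | 81-84% | about 79-80% | 89% |
| 120/90/50/30/25/15 | 36/0.1794 = 201 | 69-71% | about 70% | 83% |

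The proportion-scale interval gains power partly by exceeding its nominal error: at a true 90%, its one-sided error for 100/80/60/40/30/20 is about 5%, against 2.5%.

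**3. Centres as random clusters of 55.** Design effect = 1 + (55 − 1) × ICC; effective n = 330 / design effect. Power is by the normal approximation and the exact binomial at the effective n.

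| ICC | Design effect | Effective n | Power |
|---|---|---|---|
| 0.001 | 1.05 | 313 | 89-91% |
| 0.005 | 1.27 | 260 | 84% |
| 0.01 | 1.54 | 214 | 73-75% |
| 0.02 | 2.08 | 159 | 58-61% |

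The spare 4% is used up at an ICC of about 0.001 to 0.002.

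**4. Six clusters, even with no clustering.** Simulation of six centres of 55 at ICC 0, with the standard error taken from the spread of the six centre proportions:

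| Interval | Power at 0.95 | One-sided error at 0.90 |
|---|---|---|
| z, proportion scale | 95% | about 7% |
| z, logit scale | 88% | 4.8% |
| t(5), proportion scale | 87% | about 3.4% |
| t(5), logit scale | 69% | 2.0% |

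Of these four, only the logit-scale t(5) interval keeps its error within 2.5%, and its power is 69%.

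**The case against.** A reader might infer that 330 simply fails to deliver 90% power. The documents do not support that. The arithmetic of 330 is correct, and every loss shown above depends on something the article does not give: an ICC, centre sizes, centre weights or an interval method. With fixed centres of near-equal size, power stays at about 93%.

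The design-effect figures are open to a further objection. The model is "adjusted by the centre with cluster robust SEs". If that means a fixed effect for each centre, inference is conditional on the six hospitals and between-centre variance does not enter the standard error. With centre indicators in the model, the residuals also sum to zero within each centre, so a sandwich estimator clustered on centre collapses instead of inflating. The figures in step 3 therefore apply only if centres are treated as a random sample.

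Two readings are inferred, not stated: that the cluster is the centre, and that balancing means equal centre weights. Both are natural. The t(5) result also depends on scale: 69% on the logit scale should not be quoted without 87% on the proportion scale. Finally, the article condenses a fuller protocol, where weights and interval method may be set out.

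All of this limits how much power can be said to be lost. It does not remove the mismatch. The article states a power figure and an analysis, and the figure was derived for another analysis. Equal recruitment, which the favourable case needs, is not secured by consecutive enrolment without centre targets.

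**Conclusion.** The point stands in a limited form. The claim of at least 90% power per tumour type is correct for a simple binomial proportion and unsupported for the analysis described. It holds if the six centres are fixed and recruit nearly equally. It is not shown otherwise, and the margin for departures is only about 4% of the sample.

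The size depends on the assumptions: about 70-89% for the two uneven recruitment patterns with fixed, equally weighted centres; about 84%, 73-75% and 58-61% at ICC 0.005, 0.01 and 0.02 with random clusters of 55; 69-87% for t(5) limits on six equal centres at ICC 0. These are separate illustrations under assumed inputs, not estimates of this study's power. All use one-sided 0.025 per tumour type, as the Sample size section does.

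**What to change.** In the Sample size section, do one of the following:

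- Restate the power at n = 330 per tumour type for the analysis in the Statistical analysis plan section. Give the assumed ICC, centre sizes, centre weights and interval method (scale and reference distribution), and show the power over a plausible range.
- State that the 90% figure applies only if the six centres are treated as fixed and recruit in near-equal numbers.

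Either way, say whether the cluster is the centre and what balancing over centres means, since the power cannot be calculated without both.

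The cost is wording, a short calculation and probably a less favourable stated power. No extra patients are needed. A patient-weighted estimate could be added as a sensitivity analysis. Making it primary would recover precision but let large centres dominate; equal weighting is defensible given the aim of covering diverse centres, so that choice belongs to the sponsor.

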### Statistical analysis plan

We will fit a logistic regression model to the binary outcome of plan acceptability adjusted by the centre with cluster robust SEs. We calculate the overall marginal proportion estimate balanced for the centre, to calculate the robust CI that maintains the family-wise error rate at 0.05. An additional analysis will investigate the inter-rater agreement for the plan. For each cancer, this will be assessed by calculating the kappa statistic between the first two expert raters assessing plans, so excluding the conditional third rating.

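### On its natural reading, the primary analysis adjusts for centre and clusters on the same six centres, so the planned standard error is zero and the confidence interval cannot support the 90% rule

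*Protocol article*

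**What the plan says.** The protocol article's Statistical analysis plan section states: "We will fit a logistic regression model to the binary outcome of plan acceptability adjusted by the centre with cluster robust SEs". It continues: "We calculate the overall marginal proportion estimate balanced for the centre, to calculate the robust CI", and says that this interval "maintains the family-wise error rate at 0.05". It names no cluster unit apart from centre, no reference distribution and no small-sample correction.

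The Abstract (Methods) places the study in "six public sector cancer hospitals in India (n=2), Jordan (n=1), Malaysia (n=1) and South Africa (n=2"), which makes six centres.

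The Sample size section shows what the interval is for. Each tumour cohort is "calculated based on an overall 95% plan acceptability rate" and is to give "at least 90% power that the lower confidence limit for the acceptability plan will be greater than 90" per cent, "assuming alpha=0.05 (or one-sided 0.025) and a binomial distribution". The result is about 330 patients per tumour. The lower confidence limit is therefore the quantity on which each tumour's conclusion rests.

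**The concern.** Both adjusting for centre and balancing over centre point to centre terms in the logistic model. Each patient contributes one assessed automated plan, so there is no repeated measurement within patients for the clustering to address. The natural reading is therefore centre as a model term and centre as the cluster. These two choices cannot be combined. The centre terms absorb exactly the between-centre variation from which a centre-clustered sandwich estimates its variance.

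The rule that the lower limit must exceed 90% decides whether the acceptability objective is met, and the Dissemination section ties release of the software to meeting the objectives. An interval that cannot be computed as written leaves that rule without its stated error control. It also invites a choice of variance method once the data are known.

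**Working it through.** **Inputs from the article.** Six centres; about 330 patients per tumour; reference rate 90%; expected rate 95%; one-sided 0.025; at least 90% power. **Assumed, because the article gives neither:** 55 patients per centre (330/6), and intracluster correlations (ICC) of 0 to 0.05.

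**1. The plan's own figure.** With an exact binomial rule at n = 330, success needs at least 308 acceptable plans.
- P(X ≥ 308 | 330, 0.90) = 0.0224.
- P(X ≥ 308 | 330, 0.95) = 0.930.

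The stated 330 with at least 90% power is reproduced. The sample size is sound under its own independent-binomial assumption.

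**2. Centre terms with clustering on centre.** The cluster-robust variance is V = A⁻¹BA⁻¹. Here A is the information matrix, B = Σ_c u_c u_c′, and u_c is the sum of the score contributions in centre c. With a term for every centre, the likelihood equations are Σ_{i in c}(y_i − p_c) = 0 for each c. Every u_c is then 0, so B = 0 and V = 0. No ICC or centre size enters this result. A G/(G−1) factor or a t quantile does not help, since any multiple of zero is zero.

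**3. Numerical check.** Take 54, 53, 52, 51, 50 and 48 acceptable plans of 55 in the six centres. The total is 308 and the balanced proportion is 308/330 = 0.9333.
- Centre terms, clustered on centre: fitted SE = 6e-17, so both limits equal 0.9333.
- Centre terms, model-based: Σx(55 − x) = 54 + 106 + 156 + 204 + 250 + 336 = 1106. SE = √[1106/(55³ × 36)] = 0.0136. The observation-level (HC0) SE is the same.
- No centre terms, clustered on centre: squared deviations from the mean of 51.33 sum to 23.33. SE = √[(6/5) × 23.33]/330 = 0.0160.

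**4. What a zero-width interval does to the rule.** Success requires only more than 297 of 330. P(X ≥ 298 | 330, 0.90) = 0.473, against 0.025.

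**5. If there are no centre terms.** Simulation with 200,000 runs per scenario, beta-binomial centre effects, equal centres and a logit-scale interval. The first two result columns give the chance of passing at a true rate of 90% (nominal 2.5%). The last gives power at a true 95%.

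| ICC (assumed) | Normal quantile | t on 5 df | Power at 95%, t on 5 df |
|---|---|---|---|
| 0 | 4.8% | 2.0% | 69% |
| 0.02 | 5.7% | 2.5% | 40% |
| 0.05 | 6.9% | 3.2% | 28% |

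On this reading the interval is too narrow with normal quantiles and roughly correct with t on 5 df, at a large cost in power.

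**6. The replacement interval.** Centre terms with a model-based SE, equal centres, true rate 90%, ICC 0: false pass is 2.3% on the logit scale and 3.7% with a symmetric interval on the proportion scale. A score interval, computed here on the pooled count, also gives 2.3%. If centres are instead regarded as a sample from a wider population, the logit-scale figure rises to 8.1% at an assumed ICC of 0.02.

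**The case against.** **The cluster unit and the model structure are inferred.** The article attaches centre to the adjustment and does not say what the clusters are. An international panel scores the contours, and ratings could be correlated within reviewers. With 15 assumed reviewer groups as clusters, the SE is about 0.013, not zero. Nor does the section say that each tumour has its own model. A pooled model with centre and tumour main effects, clustered on centre, gave a median SE of about 0.010 against 0.013 model-based. This objection stands as a limit. The zero is certain only for a per-tumour model with centre as both term and cluster. That remains the natural reading: reviewers are never offered as clusters, and the sample size is set per tumour.

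**Nobody would report a zero-width interval.** This also stands. A reader might infer that the trial would run a 47% false-positive rate. The documents do not support that as a forecast. The figure shows only what the rule becomes if applied literally. The realistic harm is an unplanned change of method.

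**The too-narrow branch needs normal quantiles.** A reader might infer that error control fails on every reading. The article states no reference distribution, and such detail is commonly left to a full analysis plan. With t on 5 df the error is about 2 to 3% with equal centres. That branch is therefore conditional.

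**Fixed centres narrow the inference.** The Introduction and Dissemination sections look to wider use. This is a fair point, and the fix has to state its target.

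**Conclusion.** The point holds for the natural reading: one model per tumour, centre terms included, standard errors clustered on the same six centres. The cluster-robust SE of the centre-balanced proportion is then zero by algebra, whatever the ICC or centre sizes. The planned interval cannot serve the 90% rule or deliver the stated error control. Its practical consequence is an analysis that must be re-specified after the data are seen.

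Without centre terms, the concern is conditional on normal quantiles with no small-sample correction. False pass is then about 5 to 7% against 2.5% (logit scale, equal centres, assumed ICC 0 to 0.05).

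The sample size of about 330 is not in error on its own assumptions. A full analysis plan, not shown, may name another cluster unit or a correction. The published wording should still be changed.

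**What to change.** In the Statistical analysis plan section:

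1. Keep the centre terms and the centre-balanced proportion, fitted per tumour.
2. Replace the cluster-robust SE with a model-based or observation-level (HC) SE, preferably with the interval formed on the logit scale, or use a stratified score interval.
3. State that the primary inference is to these six centres.
4. Report the between-centre spread beside the primary result.
5. As a secondary analysis, fit the model without centre terms, with a small-sample-corrected cluster-robust SE and t on (centres − 1) degrees of freedom.

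If another cluster unit was intended, name it.

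The cost is a few sentences and a few lines of code, with no change to recruitment. There are two downsides. The primary interval does not cover variation to new centres. The secondary analysis has power well below 90%: about 69% at ICC 0 and 40% at an assumed ICC of 0.02, on the logit scale with equal centres.

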### Completion of participant follow-up

Participants have no further follow-up after their RT CT planning scan. Clinical management is as per the centre’s standard of care.

### Patient and public involvement

Patient partners have directly informed the research question, and cancer types chosen. The need for inclusion of AI and this study across LMIC partners has been defined through three international global RT workshops between 2017 and 2019, attended by the chief investigator (AA) at The European Organization for Nuclear Research, and in the UK and Botswana. As well as patient partners, attendees included clinical, academic and policy stakeholders from LMICs, including Ghana, Botswana, South Africa, Nigeria, Zambia and Jordan

With respect to study design, patient partners have highlighted that patient follow-up in LMICs can be challenging, with very low rates of follow-up following treatment. This has, therefore, informed the primary outcome measure of ‘RT plan acceptability’ as a measure of treatment quality without the necessity for ongoing follow-up. Patients will be treated using the current standard of care to avoid any delays, with the appraisal of automated plans occurring offline but using the RT CT planning scan that is acquired as part of the standard treatment process

Patients will be involved in the dissemination strategy. The patient-involvement coordinator (JT) will work with community engagement and involvement partners in each of the participating countries to develop a programme for dissemination of results.

### Ethics

The protocol has received ethical approval from University College London (UCL) Research Ethics Committee and each of the six recruiting sites’ Institutional Review Board (Institutional Ethics Committee, Tata Memorial Hospital; Institutional Ethics Committee, Tata Medical Centre; University of Malaya Medical Research Ethics Committee; King Hussein Cancer Center Institutional Review Board; Stellenbosch University Health Research Ethics Committee; University of Cape Town Health Research Ethics Committee). International sites will comply with the principles of GCP as laid down by the ICH topic E6 (R2) and other applicable national regulations.

Although there will be no clinical impact of the intervention or risk to the patient as they will continue to be treated according to the standard treatment pathway and not receive any additional imaging intervention or treatment, protections have been put in place for the use of pseudonymised CT scans and treatment planning details stored as DICOM files. Patients will be enrolled with written informed consent.

## Dissemination

If the study objectives are met, the AI-based software will be offered as a not-for-profit web service to public sector state hospitals in LMICs. We anticipate this will support rapid adoption into daily practice and facilitate expansion of high-quality RT in these countries. This, in turn, will improve access, and affordability of this critical treatment option, and therefore, also improve survival and the quality of life of patients with cancer globally.
